Eligible participants will be randomly assigned to one of the two treatment modalities stratified by tumor stage and hospital and will be unblinded about the treatment they will be receiving in the target trial. In an open-label, multi-institutional, randomized, two-arm phase III trial, Kitano and colleagues randomly assigned patients with stage II–III colon cancer to either laparoscopic or open colectomy one day before surgery (Kitano et al. 2017). Similar to this RCT, our target trial study would randomize the patients one day before the day of surgery, but with a three-months grace-period to allow for successful implementation of the surgical treatment modalities. The incorporation of a grace-period into a pragmatic trial design prevents ill-defined interventions and improves the use of observational data by expanding the pool of patients who can be included in emulated studies while helping capture real-world clinical practice (Hernan et al. 2016; Hernan and Robins 2016). Accordingly, in our emulated study, patients will be classified into either the laparoscopic colectomy group or the open colectomy group for the treatment of colon cancer within the specified grace-period according to the surgical procedures performed as documented in the patients’ cancer registry records. In contrast to the randomized allocation of patients described in the hypothetical RCT mentioned above, the patients in the emulated trial will not be assigned randomly to one of the treatment modalities. Nevertheless, randomness will be emulated by controlling confounders at baseline using inverse-probability weighting methods and/or via cloning of patients in both arms (Hernan and Robins 2016).

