#### Statistical analysis

Patient characteristics will be summarized using frequencies and percentages for categorical variables, whereas means and standard deviations or medians and interquartile ranges will be used for continuous variables, depending on their distributions.

We will use the clone-censor-weight design to emulate the hypothetical target trial (Hernan and Robins 2016). Since each patient will be eligible for one of the two surgical treatment modalities during the three-month grace-period, we will first clone (copy) each patient record, and each clone will then be allowed to enter both treatment arms for the duration of the grace-period regardless of the surgical modality they will actually receive later. This will emulate randomization in the specified target trial and addresses the issue of confounding at baseline, as both treatment arms are identical in terms of baseline patient characteristics. Cloning also offers the opportunity for even distribution of survival times (before surgery, for the entire grace-period or any early deaths that may occur before treatment) between the two surgical treatment modalities, allowing us to circumvent the problem of immortal time bias (Hernan and Robins 2016). In the next step, we will censor clones over time if non-compliance with the initially assigned treatment strategy is detected from that timepoint onward. This implies that we will censor clones assigned to laparoscopic colectomy (including converted colectomy) but whose records indicate that they underwent open colectomy within the grace-period, or vice versa. The censoring times will be defined corresponding to the time of each censoring event and will be incorporated into the weighting model described below. Figure2 provides all possible treatment paths and the respective censoring mechanism of the trial emulation for both treatment and outcome models.

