**Fig. 2 Fig2:**
[figure not shown]
Definition of outcome and survival times for each patient in each emulation arm

The informative censoring (and hence associated selection bias) induced by the implementation of artificial censoring will be adjusted via inverse-probability censoring weighting (IPCW). This will reflect the likelihood of being compliant (uncensored) with the assigned treatment strategy given the confounding factors. However, prior to cloning, an inverse-probability of treatment weighting (IPTW) on the uncloned (original) population will be estimated with the aim of assigning larger weights to patients who will be less likely to undergo laparoscopic colectomy, given the individual constellation of confounding factors. These weights (IPTW and IPCW) will be estimated by running separate models using a logit function and later combined by multiplying both weights. This single combined weight will later allow us to determine an unbiased causal effect of laparoscopic versus open surgical treatment. We will then use absolute standardized differences within ≤ 10% as an indicator of adequate balance of the covariates (confounders) between the two treatment arms. If there will be evidence of imbalance, the weights at the 1st and 99th percentiles will be trimmed to reduce the effect of extreme weights. This will be achieved by replacing all weight values that are below the 1st percentile with the 1st percentile value and by replacing all weight values above the 99th percentile with the 99th percentile value.

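### Multiplying the treatment weight by the censoring weight in the cloned analysis counts the choice of operation twice and, with the conventional treatment weight, reverses measured confounding in a direction the protocol does not reveal

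*Protocol article*

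**What the plan says.** The Statistical analysis section copies every patient into both arms and says of this step: "This will emulate randomization in the specified target trial and addresses the issue of confounding at baseline, as both treatment arms are identical". Clones are then censored when the record shows the other operation; the plan "will censor clones assigned to laparoscopic colectomy (including converted colectomy) but whose records indicate that they underwent open colectomy within the grace-period", and the reverse for the open arm.

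The text after Figure 2 introduces IPCW for this artificial censoring: "This will reflect the likelihood of being compliant (uncensored) with the assigned treatment strategy given the confounding factors". It then adds a second weight: "prior to cloning, an inverse-probability of treatment weighting (IPTW) on the uncloned (original) population will be estimated". That second weight models which operation a patient receives, and the protocol describes its purpose as "assigning larger weights to patients who will be less likely to undergo laparoscopic colectomy, given the individual constellation of confounding factors". On combining the two weights it says: "These weights (IPTW and IPCW) will be estimated by running separate models using a logit function and later combined by multiplying both weights". The single combined weight is said to give an unbiased causal effect. If standardised differences exceed 10%, the stated response is to trim the weights at the 1st and 99th percentiles.

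The section on the design of the target and emulated trials leaves the roles of the two devices open, describing "controlling confounders at baseline using inverse-probability weighting methods and/or via cloning of patients in both arms". In Table 1, eligibility for the emulated trial requires a laparoscopic or open colectomy within 90 days of diagnosis.

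**The concern.** IPCW in a clone-censor-weight design and IPTW in a conventional cohort are two routes to the same correction. Cloning balances the arms at time-zero. Imbalance enters when clones are censored, and here that happens because the patient received the other operation. A weight for staying uncensored already accounts for who receives which operation. A further weight for who receives which operation accounts for it again.

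The combined weight enters the Royston-Parmar model, from which the hazard ratio, risk differences and RMST differences are obtained. Bootstrap intervals built with that weight would be centred on the biased value.

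**Working it through.** **Inputs from the protocol.** Surgery within 90 days is an eligibility condition (Table 1). The censoring trigger is receipt of the other modality. IPCW is described for artificial censoring only; no loss-to-follow-up weight is mentioned. The weights are multiplied. The protocol gives no sample size, laparoscopic share, mortality or strength of selection, so there is no planned figure to reproduce, and every such number below is an assumption.

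**Algebra (no assumed figures).** Let f(X) be the covariate distribution of the eligible cohort and e(X) the probability of laparoscopy given X. Everyone is operated on within the grace period, so P(uncensored in the laparoscopic arm | X) = e(X) and P(uncensored in the open arm | X) = 1 - e(X). With weights built up over time, the IPCW among those who follow the arm averages 1/e(X) or 1/(1 - e(X)) over surgery dates.

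| Weight | Laparoscopic arm | Open arm |
|---|---|---|
| None | f(X)·e(X) | f(X)·(1 - e(X)) |
| IPCW only | f(X) | f(X) |
| IPTW × IPCW, IPTW = 1/P(modality received) | f(X)/e(X) | f(X)/(1 - e(X)) |
| 1/e(X) for every patient × IPCW | f(X)/e(X) | f(X)/e(X) |

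The third row reverses the first. The fourth is balanced, but in a population other than the eligible cohort.

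**Two-level example (assumed).** Half the patients are low-risk and half high-risk; P(laparoscopy) is 0.5 and 0.2; five-year mortality is 0.20 and 0.45 whichever operation is done.

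- Unweighted: the high-risk share is 0.2/0.7 = 0.286 in the laparoscopic arm and 0.8/1.3 = 0.615 in the open arm. Mortality is 0.271 and 0.354, a difference of -0.082.
- IPCW only: the high-risk share is 0.5 in both arms. Mortality is 0.325 in both, a difference of 0.
- Product: the laparoscopic arm has masses 1/0.5 = 2 (low) and 1/0.2 = 5 (high), a high-risk share of 5/7 = 0.714. The open arm has 1/0.5 = 2 and 1/0.8 = 1.25, a share of 1.25/3.25 = 0.385. Mortality is 0.379 and 0.296, a difference of +0.082.
- Product with P(laparoscopy) swapped to 0.2 and 0.5: -0.082.
- Product with P(laparoscopy) equal in both groups: 0.

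**Simulation under a true hazard ratio of 1.00 (assumed).** One covariate, about 26% laparoscopic, about 23% five-year mortality. The covariate's hazard ratio for death per SD is 1.49, or 1.65 in the rows with an odds ratio of 0.61 or 1/0.61. Ranges cover separate runs.

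| Odds ratio for laparoscopy per SD of worse prognosis | One weight | Product | Product, trimmed 1/99 |
|---|---|---|---|
| 0.90 | 1.00 | 1.04 | 1.04 |
| 0.70 | 1.00 | 1.14 to 1.16 | 1.11 to 1.13 |
| 0.61 | 1.00 | 1.28 | 1.20 |
| 1/0.70 | 1.00 | 0.86 | 0.88 |
| 1/0.61 | 1.00 | 0.77 to 0.78 | 0.81 |

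With the product, the covariate difference between arms is about +0.36 SD at an odds ratio of 0.70 and about +0.53 SD at 0.61.

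A separate clone-censor simulation used weights estimated from the data and log-odds of selection of 0.2, 0.4 and 0.7 per SD. After trimming, differences of 0.14, 0.26 and 0.41 SD remained, all above the plan's 10% limit. Stabilising the IPTW barely changed the hazard ratio (for example 1.37 against 1.38).

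**The case against.** **Direction.** A reader might infer that the plan would make a null effect look like harm from laparoscopy. The documents do not support that. The Introduction mentions patient selection between the modalities but not which operation receives the better-prognosis patients in this registry. Selection the other way turns a null into apparent benefit, and with no selection on prognosis there is no bias.

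**Meaning of the IPTW.** The stated aim of giving larger weights to patients less likely to have laparoscopy does not fit the conventional weight in open patients, where a lower e(X) gives a smaller 1/(1 - e(X)). Read literally, it could mean 1/e(X) carried by both clones. The arms then balance and nothing is reversed, but the estimate refers to a population weighted towards patients unlikely to have laparoscopy. This reading is possible, though it is not the usual meaning of IPTW. The text would still need correcting.

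**Safeguards.** The standardised-difference check would probably expose the imbalance, and trimming reduces the bias. But trimming is the only stated response, and it treats extreme weights when the fault lies in the form of the weight. The comparator analyses (adjusted Cox and doubly robust) would make a large discrepancy easier to notice, but they do not repair the main estimate.

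**Exactness.** The text on cloning also speaks of deaths before surgery. If such patients are kept, P(uncensored | X) is only approximately e(X); the double correction remains.

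**Condensed article.** A fuller plan may give more detail, but the multiplication is an explicit instruction here, not an omission.

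**Conclusion.** The concern stands as an error in the weight as written. Under the conventional IPTW, the product standardises the arms to f(X)/e(X) and f(X)/(1 - e(X)), so measured confounding is reversed. This needs no assumed numbers beyond e(X) being related to prognosis, the situation in which weighting matters.

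The direction cannot be known from the documents. The size depends on the strength of selection. Over the assumed odds ratios of 0.90 to 0.61, a true null becomes about 1.04 to 1.28, or 1.04 to 1.20 trimmed; with selection reversed at 1/0.70 it becomes about 0.86, or 0.88 trimmed. Under the alternative reading, 1/P(laparoscopy) for everyone, the fault is the milder one of a shifted target population. Under either reading, the claim that the combined weight yields an unbiased effect for the eligible cohort does not hold. This should be corrected before the analysis is run.

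**What to change.** In the cloned analysis, use one weight: the IPCW for artificial censoring, estimated on the cloned data and written out as a formula. If loss to follow-up is also to be weighted, multiply by a separate weight modelled on that event. Delete the pre-cloning IPTW step and the multiplication. Apply the 10% standardised-difference check to the weighted, uncensored clones at the end of the grace period. Remove the and/or wording in the design section, so that it is clear that cloning balances the arms at time-zero and IPCW maintains that balance through censoring.

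The cost is one rewritten paragraph and less code. No further data are needed.

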Finally, we will use an inverse-probability weighted Royston-Parmar parametric survival model (RPpsm) to estimate an unbiased causal effect of laparoscopic versus open surgical treatment on OS via hazard ratio. If incorporating the final weight (derived from IPTW and IPCW) into the RPpsm will not be achieved, we will alternatively use weighted pooled logistic regression to model the outcome. When the event of interest (death from any cause) occurs, that event is considered to be an event solely in the patients’ originally planned treatment arm, in which each patient is initially consistent and remains uncensored at the point in time when the event occurs. On the other hand, the cloned records will be censored at that exact time the event occurs, which is accomplished by censoring indicators. Using weighted RPpsm postestimation tools, OS will be estimated using differences in absolute risk and restricted median survival (RMST) at 1-, 3-, and 5-years and up to 1-, 3-, and 5-years, respectively. To account for the weighting to be applied, point estimates will be accompanied by 95% confidence intervals via non-parametric bootstrapping with 500 replicates. A weighted Kaplan-Meier method will be used to compare time-to-event curves over a 60-months period according to surgical treatment modality. We will compare our results with estimates from the literature. We make use of the CERBOT (Comparative Effectiveness Research Based on Observational Data to Emulate a Target Trial) tool (see Additional file 1) in our emulation process (Zhang et al. 2024).

It is crucial to handle missing data properly to obtain more powerful models resulting in better estimates (Mbona et al. 2023). We will use multiple imputation via the chained equations method to impute missing values in covariates, assuming that observed missing values are missing at random (White and Royston 2009). In the literature, this method is also referred to as “multivariate imputation with sequential regression” and “imputation using fully conditional specifications” (Raghunathan et al. 2001; van Buuren et al. 1999). All variables of the analysis dataset, including the outcome variable, will be used for the imputation model and ten datasets (m = 10) will be imputed.

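### Residual imbalance triggers weight truncation as the only stated response, although truncation cannot repair a weight model that under-corrects and helps only when extreme weights cause the imbalance

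*Protocol article*

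**What the plan says.** All of this stands in the protocol article, Methods, Statistical analysis, mostly in the paragraph after the Fig. 2 caption.

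- **Weights.** A treatment weight (IPTW) is estimated on the uncloned population and a censoring weight (IPCW) handles the artificial censoring: "These weights (IPTW and IPCW) will be estimated by running separate models using a logit function and later combined by multiplying both weights".
- **Balance check.** "We will then use absolute standardized differences within ≤ 10% as an indicator of adequate balance of the covariates (confounders) between the two treatment arms".
- **Response to failure.** "If there will be evidence of imbalance, the weights at the 1st and 99th percentiles will be trimmed". The purpose given in the same sentence is to damp extreme weights. The trimming is winsorising: no patient is dropped, and the upper tail is handled by "replacing all weight values above the 99th percentile with the 99th percentile value", with the mirror rule at the 1st percentile.
- **Claim.** "This single combined weight will later allow us to determine an unbiased causal effect of laparoscopic versus open surgical treatment". The outcome model repeats it: "we will use an inverse-probability weighted Royston-Parmar parametric survival model (RPpsm) to estimate an unbiased causal effect".

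Table 1 and the section on sensitivity and comparator analyses list complete cases, inclusion of T4 disease and E-values, then two comparators: a DAG-guided Cox model and a doubly robust analysis. None of them is described as varying the truncation.

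**The concern.** The trigger and the remedy belong to different problems. The trigger is covariate imbalance. The remedy, by the article's own statement of purpose, addresses extreme weights. Extreme weights with good balance trigger nothing, and imbalance without extreme weights triggers truncation.

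Truncation also has a direction. Capping the weights is a step from full weighting toward equal weighting, and equal weighting gives the crude comparison. If balance failed because the weight model corrects too little (a missing covariate, a non-linear effect entered too coarsely), the capped patients are often the ones doing the correcting.

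At stake is the primary estimate. The primary outcome model relies on the combined weight to control confounding and selection; regression adjustment on top of weighting is kept for a comparator. A failed check could be answered by a step that leaves measured confounding in place or adds to it, while the result is still described as unbiased.

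**Working it through.** **Inputs from the article:** the 10% limit, the 1st and 99th percentiles, winsorising, and logit weight models. The article states no figure on this point that could be reproduced.

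**Inputs assumed, because the article gives none:** n = 1,000, 3,000 or 10,000; five baseline confounders (three continuous, two binary); confounding strength 0.5, 1.0 or 1.5; a linear outcome with true effect 0; one treatment decision with unstabilised weights, not the IPTW × IPCW product after cloning. There were 150 to 400 replicates per scenario.

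**Formulas.**
- Weight: w = 1/p for laparoscopic and 1/(1 − p) for open, with p the fitted probability of laparoscopic surgery.
- Truncated weight: w_t = min(max(w, P1), P99).
- Standardized difference: SMD = (weighted mean in arm 1 − weighted mean in arm 0) / √((s₁² + s₀²)/2).
- Effect: difference in weighted outcome means. The true effect is 0, so the mean estimate is the bias.

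**Results.** Arrows run from untruncated to truncated; n = 3,000 and strength 1.0 unless stated.

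| Situation | Max abs. SMD | Bias | Within 10% after truncation |
|---|---|---|---|
| Correct model, all replicates | 0.048 → 0.096 | 0.002 → 0.159 | 58% (97% before) |
| Trigger met, confounder dichotomised | 0.339 → 0.366 | 0.325 → 0.407 | 0% |
| Trigger met, confounder omitted | 0.486 → 0.477 | 0.250 → 0.355 | 0% |
| Positive quadratic term omitted (over-correction) | 0.325 → 0.092 | −0.329 → +0.021 | 69% |
| Correct model, n = 10,000, strength 1.5, trigger met | 0.140 → 0.209 | −0.125 → 0.334 | 0% |

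With a correct model at n = 1,000 and the trigger met by chance, the maximum fell from 0.148 to 0.117 on average and worsened in 49% of replicates.

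**Reading the table.**
1. *Under-correction (rows 2 and 3).* With the omitted confounder the largest difference hardly moves, but the mean absolute SMD rises from 0.112 to 0.130. As a share of the crude bias, the remaining bias goes from 0.250/1.366 = 18% to 0.355/1.366 = 26%. For the dichotomised confounder it goes from 0.325/1.372 = 24% to 0.407/1.372 = 30%.
2. *Over-correction (row 4).* The untruncated bias has the opposite sign to the crude bias, so a step toward the crude estimate is a step toward the truth.
3. *Direction.* In every scenario the mean truncated estimate lay nearer the crude one. In the runs on under-correction and an omitted negative quadratic term, where it was counted, this held in 100% of triggered replicates.
4. *The type of misspecification does not settle the matter.* With a negative quadratic term omitted, the trigger was met in 2% of replicates; these were over-corrected (bias −0.202, crude +1.214), and truncation took the maximum from 0.129 to 0.051. A separate simulation found under-correction from the same kind of omission, and balance worsened (0.117 to 0.151). There the dichotomised confounder was unchanged (0.34 to 0.34), the positive quadratic case improved (0.214 to 0.033), and under-correcting models regained the limit in 0–1% of triggered replicates.

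**The case against.** **Truncation can be the right response.** The article gives its purpose as damping extreme weights, and where these cause the imbalance the simulations bear it out. A reader might infer from the direction of the pull that truncation always makes balance worse. That does not hold: row 4 of the table contradicts it. Nor does a failed check prove misspecification. With a single confounder of slope b = 1.0 on the logit scale, a correct model and n = 1,000, 9.6% of replicates failed the limit by chance.

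**The rule acts only when the check fails.** Row 1 of the table truncates every data set, mostly ones that passed and that the plan would leave alone. The same holds for a one-confounder simulation at n = 4,000 with a correct model: truncating everything gives mean SMDs of −0.028, −0.087 and −0.188 for b = 0.5, 1.0 and 1.5, but the trigger fires in 0%, 0.6% and 16% of replicates. At b = 1.0 all six triggered replicates (of 1,000) improved. At b = 1.5 (crude difference 1.26) 74% worsened, from 0.145 to 0.192 on average. Figures from untriggered data show direction, not the harm to expect.

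**A condensed article need not describe model building or rechecking.** This stands, and the absence of those details is not the point. The point is the conditional rule that the article does state.

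**The comparators might reveal residual confounding.** They might, but they do not replace a sound primary weight. The E-value analysis addresses unmeasured BMI, comorbidity and prior surgery, not imbalance in measured covariates.

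**Conclusion.** The concern holds in a limited form. The rule links a failed balance check to a remedy whose effect depends on why the check failed, and it does not ask why. If the weight model under-corrects, truncation leaves balance about the same or worse, adds bias toward the crude comparison and almost never restores the 10% limit. If extreme weights over-correct, it can improve both balance and bias. The rule therefore does not secure the unbiased effect that the article claims.

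A reader might go further and conclude that the primary estimate will be computed on weights made less balanced. The article does not support that: it gives no sample size, treatment prevalence, crude imbalance or weight distribution, so neither the chance of triggering the rule nor its effect here can be derived. The simulated sizes rest on a point treatment with assumed confounding; the mechanism carries over to the combined weight, the exact figures do not. The rule should be changed before the analysis, but it does not invalidate the design.

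**What to change.** Replace the conditional rule with two separate ones.

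1. **Balance.** Compute standardized differences in the weighted arms after artificial censoring, since cloned arms are identical at baseline by construction. If any exceeds 10%, respecify the treatment or censoring weight model (for example non-linear age terms, or interactions with treatment period or hospital type) and recheck, before looking at outcomes.
2. **Extreme weights.** Let the weight distribution trigger truncation, for example a very large maximum or a mean of stabilised weights far from 1. Report balance again after any truncation and show the untruncated estimate alongside.

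Describe the effect as unbiased only under stated conditions, including a correct weight model. The cost is a few sentences and a little more model checking; no new data are needed.
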